### 12. Standardization

A study manual was prepared based on the experience gained from the pilot work, which outlines the protocols for assessments; injection, therapy, and pain management. The manual was discussed at the face-to-face meetings in 2005. Consensus was reached on key points and it was revised in December 2005

Regular conference calls and an annual meeting are planned to further ensure consistency across sites.

Individual patient tracking sheets ensure that data collection is complete at each time point.

### 13. Data Management

All data will be kept confidential using a coding system unique to each hospital. With the input of a medical information specialist from headquarters, a collaborative research site will be established on the Shriners intranet system to facilitate an electronic interface for data collection and data transfer.

Pain scores and medication dosages will be extracted from the medical record and transferred to a customized data collection form available on the intranet site. Hospitals will send the data collection forms by courier to the project manager at the Montreal Hospital where trained personnel will enter all the data into the Access database. Paper copies of the questionnaires will record the pertinent scores and the completed questionnaires (identified by study number only) will be sent by courier to the lead hospital and treated similarly.

This database will include some validation processes to ensure the quality of the data. Any doubtful data will be checked with the person responsible at the site where it occurred, and changes to the database will be documented. A single person at the Lead hospital will do the data entry to ensure reliability of the process. The data analysis will be performed by bio-statistician consultants to the project.

### 14. Statistical Analysis

Descriptive statistics will be calculated for all outcome variables and all relevant baseline variables. The data will be presented in summary tables, graphs, and listings to give an overview of the outcome and efficacy findings. The mean, median, standard deviation, and range of each variable and its change from baseline, measured on a continuous scale, will be presented by treatment and visit. Frequency tables will be provided for categorical variables by treatment and visit.

There are three primary outcomes: pain measured by the FPS-r or NRS, requirements of pain medication, and the quality of life using the PedsQL. The primary analysis for the pain will be performed during the post-operative (5–10 days) period as well as the mid-distraction phase. The primary analysis for the pediatric quality of life will be performed at mid-distraction and the mid-consolidation phase before the removal of the fixator. The primary analysis will be conducted using T-tests for continuous variables and chi-square and Fisher exact tests for categorical variables.

An interim analysis will be performed when 75 patients (1/2 the estimated sample size) have been enrolled, using the Obrien-Fleming group-sequential stopping rule. [82,83]

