##### A. Paralytic effects

Botulinum toxin is a pre-synaptic neuromuscular blocking agent. It produces temporary chemical denervation by blocking the release of acetylcholine, thus, causing muscle relaxation. BTX-A acts on all cholinergic nerve terminals, including those of motor neurons, preganglionic sympathetic and parasympathetic neurons and postganglionic parasympathetic nerves. The molecular mechanism of inhibition of acetylcholine release is a multistep process that has been very well described [51].

Muscle weakness occurs within a few days to 1 week after local injection, peaks within 2 weeks for several weeks, and then plateaus in milder form (the desired clinical effect) before gradually returning to baseline [51]. The effects of BTX-A are dose related. Recovery from the toxin-induced paralysis involves resprouting of terminals from the axon, followed by slow recovery of the neuron's ability to release acetylcholine. The clinical effects last 3 to 4 months after each injection [51].

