##### iv. Analgesic effect through alteration of autonomic function

Blood flow is clearly related to inflammation and ischemic pain and is probably involved in the sensitization of nociceptors. Autonomic neurons alter regional blood flow by controlling the smooth muscle walls of small arterioles. BTX-A may block some of the autonomic vascular control functions and at the same time may alter the release of a variety of non-ACh agents that also affect blood flow. Finally, autonomic function mediated by the release of ACh is associated with both emotional behaviour and stress through complex CNS circuity. BTX-A may alter the global perception of pain and or the patient's overall response to pain through this linkage [67].

Although the analgesic properties of BTX-A could have tremendous potential in a wide variety of clinical problems [69-71]], we were able to find only one study on the effects of BTX-A in relieving post-operative pain in orthopaedic procedures and none in the context of limb lengthening. In a double-blinded, placebo controlled trial [72], Barwood et al. reported profound anti-nociceptive activity of BTX-A injection when administered prior to adductor-release surgery in children with cerebral palsy. The analgesic effect was so dramatic that the trial was terminated early. Children treated with BTX-A had a reduced need for narcotic analgesics, were discharged earlier, and had better outcomes than the placebo group.

The objective of the current multi centre clinical study is to assess if the use of Botox does alleviate pain for children in the early post op period during distraction osteogenesis. This protocol addresses the issues of both pain and muscle spasm through the use of BTX-A injections.

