#### Primary statistical hypotheses

• Pain scores will be less, in those who received BTX-A, during the 5–10 days post-operative period compared to those who received saline injections (Specific aim 1).

• Pain scores will be less, in those who received BTX-A, at mid-distraction compared to those who received saline injections (Specific aim 1).

• The total amount of narcotic pain medication during the 10 days post-operative will be lower in those patients who received BTX-A than in those who received saline injections.

• Quality of life scores during mid-distraction will be higher in those who received BTX-A compared to those who received saline injections (Specific aim 2).

• Range of motion measurements and mobility scores will be improved in those who received BTX-A compared to those who received saline injections (Specific aim 3).

Primary Outcome Measures: FPS-r/NRS, PedsQL, ROM

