#### Sample size

The proposed sample size of 75 per group provides 80% power to detect an effect size of 0.45, with alpha = 0.05. The effect size of 0.45 corresponds to a difference of approximately 7.5 in the PedsQL (Ref Varni et al 2002, Varni et al 2003). This difference is smaller than that found in studies comparing children with chronic diseases to healthy children. The following table provides a range of options for sample size, using the PedsQL as an example. For a standard deviation (SD) of 15 and alpha (type I error) of 0.05, the power is as given in the first column for different values of delta (the detectable difference between the groups). The differences detected in the pilot work support the planned sample size.

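### The protocol gives two conflicting sets of primary outcomes, each implying at least five tests, with no stated order, alpha split or success rule

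*Protocol article*

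**What the plan says.** The protocol article defines the primary outcomes in two adjoining places.

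- **Section 14, Statistical Analysis.** "There are three primary outcomes: pain measured by the FPS-r or NRS, requirements of pain medication, and the quality of life using the PedsQL". On timing: "The primary analysis for the pain will be performed during the post-operative (5–10 days) period as well as the mid-distraction phase", and "The primary analysis for the pediatric quality of life will be performed at mid-distraction and the mid-consolidation phase before the removal of the fixator". The tests are separate t-tests for continuous variables and chi-square or Fisher tests for categorical ones.
- **Primary statistical hypotheses.** Five bullets cover post-operative pain, mid-distraction pain, narcotic use over 10 post-operative days, PedsQL at mid-distraction, and a combined claim: "Range of motion measurements and mobility scores will be improved in those who received BTX-A compared to those who received saline injections". The subsection then closes with "Primary Outcome Measures: FPS-r/NRS, PedsQL, ROM".

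The Sample size subsection says "The proposed sample size of 75 per group provides 80% power to detect an effect size of 0.45, with alpha = 0.05" and uses the PedsQL as its worked example. Section 14 plans one interim analysis at 75 patients with an O'Brien-Fleming rule. Section 10, on the monitoring committee, halts the trial if that analysis is statistically significant. Neither place names the outcome to which this applies.

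**The concern.** Medication is a primary outcome in section 14, is absent from the closing line of the hypotheses subsection, and is present in that subsection's own bullets. Range of motion is primary in the hypotheses subsection and not in section 14. Mobility appears only in a bullet. PedsQL at mid-consolidation is primary in section 14 only. A reader cannot tell from the document whether medication, range of motion, mobility or mid-consolidation PedsQL is primary.

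Two things are at stake. The choice between the lists could be made after the data are seen. And with several primary tests and no rule joining them, any one significant result could be reported as the trial's success. The interim stopping rule has the same gap, because it does not say which outcome has to be significant.

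**Working it through.** **1. Counting the tests.**

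| Outcome | Section 14 text | Hypothesis bullets | Merged |
|---|---|---|---|
| Pain, post-operative | 1 | 1 | 1 |
| Pain, mid-distraction | 1 | 1 | 1 |
| Pain medication / narcotics | 1 | 1 | 1 |
| PedsQL, mid-distraction | 1 | 1 | 1 |
| PedsQL, mid-consolidation | 1 | – | 1 |
| Range of motion | – | 1 | 1 |
| Mobility | – | shares the range-of-motion bullet | 1 |
| Total | 5 | 5 (6 if the last bullet is split) | 7 |

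The count would be higher if range of motion were tested by joint or visit, or if parent and child PedsQL versions were both tested.

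**2. Which alpha the sample size uses.** Inputs from the Sample size subsection: n = 75 per group, effect size d = 0.45, alpha = 0.05. Sidedness is not stated.

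Normal approximation: power = Φ(d·√(n/2) − z). Here d·√(n/2) = 0.45 × √37.5 = 2.756.

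- Two-sided 0.05: Φ(2.756 − 1.960) = Φ(0.796) = 78.7% (noncentral t: 78.2%). This matches the stated 80% within rounding; exactly 80% needs 78 per group.
- One-sided 0.05: Φ(2.756 − 1.645) = 86.7%, which does not match.
- Two-sided 0.05/5 = 0.01: Φ(2.756 − 2.576) = 57.1%, which does not match.

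The stated power therefore fits a single test at an unsplit two-sided 0.05.

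**3. Chance of at least one false positive if every test is run at two-sided 0.05.** Independent tests: 1 − 0.95^k, so 1 − 0.95^5 = 22.6% and 1 − 0.95^7 = 30.2%. Correlated tests come from a simulation of equicorrelated z-tests (1,000,000 draws). The documents give no correlation, so 0 to 0.7 is an assumed range.

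| Common correlation | 5 tests | 7 tests |
|---|---|---|
| 0 | 22.6% | 30.2% |
| 0.3 | 20.9% | 27.2% |
| 0.5 | 18.3% | 23.0% |
| 0.7 | 14.8% | 17.8% |

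These figures count false positives in either direction. For false claims of benefit alone, each test has 0.025: 1 − 0.975^5 = 11.9% and 1 − 0.975^7 = 16.2% if independent, or about half of the two-sided figures.

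**4. Power at d = 0.45 and 75 per group if alpha is split equally (Bonferroni).**

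| Tests | Alpha each | Power, noncentral t | Power, normal approx. | n per group for 80% (normal approx.) |
|---|---|---|---|---|
| 1 | 0.05 | 78.2% | 78.7% | 78 |
| 3 | 0.0167 | 63.1% | 64.1% | 104 |
| 5 | 0.01 | 55.9% | 57.1% | 116 |

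**The case against.** The strongest reply is that a journal article condenses the protocol, and that rules for multiple testing are commonly left to an analysis plan that is not shown. That stands as far as it goes. The article nowhere says that each outcome is tested at 0.05; this is inferred from the only alpha given and from a power figure that fits only an unsplit level. The absence of a multiplicity rule alone would not be a finding. But no unseen document can make two conflicting lists both true, and a plan that split alpha would no longer have the stated 80% power. The O'Brien-Fleming rule controls repeated looks, not several outcomes.

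Three stronger readings are tempting and should not be made.

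- **That the false-positive risk is 20-30%.** This is the upper part of the range. The 30% figure needs seven independent tests, and seven arises only by merging the two lists. The Discussion calls the key variables linked, which points lower. The calculation also would not apply under a rule that every primary outcome must succeed, although no such rule is stated.
- **That mid-consolidation PedsQL falls after the drug has worn off.** A reader might set the 5 cm example in the Background (7 + 50 + 75 = 132 days, about 4.3 months) against "The clinical effects last 3 to 4 months after each injection". If the five months in that example mean total frame time, mid-consolidation falls midway between day 57 and about day 150, near 3.4 months. A 3 cm lengthening gives 7 + 30 + 45 = 82 days, about 2.7 months, and any amount of lengthening is eligible. The duration statement also stands under paralytic effects, and the Background reports that pain relief can outlast weakness. The documents do not support this criticism.
- **That early pain must lead and function be demoted.** The Background does state the objective as to "alleviate pain for children in the early post op period during distraction osteogenesis". The Abstract and Discussion, however, also name functional outcome, and PedsQL is the only outcome with a power example. The order is for the investigators to justify.

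**Conclusion.** The contradiction is certain from the current text and has to be resolved: medication, range of motion, mobility and mid-consolidation PedsQL are each primary in one place and not in another. The multiplicity concern holds conditionally. If each primary test is run at two-sided 0.05 and any one success counts, the chance of at least one false positive is about 15-23% for five tests and 18-30% for seven, against a nominal 5%, with correlations of 0.7 to 0 assumed. For false claims of benefit the figures are about half. The 80% power statement describes one test at the full 0.05 and cannot be read as covering a set of outcomes among which alpha is divided.

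**What to change.** Before unblinding, by a wording amendment:

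1. Make section 14 and the hypotheses subsection agree on one list of primary outcomes and time points, and move the rest to secondary.
2. State one rule that holds the overall two-sided error at 0.05: either a fixed sequence, in an order that the investigators justify from their aims, or Holm's procedure.
3. Name the outcome to which the interim stopping rule applies.
4. Say which test the 80% power describes. Restate the power if alpha is split: about 63% for three tests or 56% for five, at effect size 0.45 under Bonferroni. Holm is never less powerful than Bonferroni, so these serve as lower bounds for it.

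The cost is mainly in what can be claimed. In a fixed sequence the first test keeps the full 0.05 and needs no extra patients on that account, but a later outcome can be claimed only if all earlier ones succeed, so the order matters. Under Holm no order is needed, but at least the first test faces a stricter level, with the loss of power shown above unless the sample is enlarged.

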### 8. Pain Management Protocol

Pain management (assessment and treatment) guidelines are described in the study manual. Post operative pain medication is delivered via either PCA or epidural up to 72 h post-op. Pain assessment will be done using a 10 point scale (either Faces Pain Scale revised or the Numerical Rating Scale) according to post-operative PCA protocols; hourly for first 4 hours, every 2 hours for next 8 hours, and every 4 hours once stable. After the PCA/epidural is discontinued, PRN medications will be ordered for pain control, nausea/vomiting, itching, and fever during hospitalization. Pain assessments will also be done whenever a patient receives a PRN medication. All of this data will be recorded in the patient's chart along with the medication dosages administered.

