### 11. Outcome Assessment

The outcome measures selected for the study relate directly to the specific aims of the project. The data collected will provide information on the pain scores, medication dosages, range of motion, flexibility, strength, mobility function, and quality of life of the patient population under study. Additional data will be collected on the patient demographics, musculoskeletal information, impact on the family during the distraction process, and motivation of the child. During the pilot study the participating hospitals finalized the selection of the outcome tools, the data collection forms of physiotherapy and nursing, as well as the timing of administration. The research coordinator at each site will ensure that the timeline is respected.

The measures will be administered pre-lengthening, pre-distraction, mid-distraction, end distraction, mid-consolidation, pre-frame removal and 3 months post-frame removal. Pain scores, medication dosages and compliance to physical therapy will be recorded daily during admission and throughout the distraction/consolidation process. A timeline as shown in Table 1 will indicate when the different variables will be measured and which tool is given at which phase of the process. The time required to complete the assessments is 20–30 minutes.

Standardized assessments chosen have been validated and are reliable. The outcome measures are described below.

The **Numerical Rating Scale (NRS**) is a reliable and valid tool that is widely used in pediatric centers as a measure of acute pain. The **Faces Pain Scale-Revised **is a reliable and valid pain scale for younger children. These tools will be used by nursing to assess postoperative pain during the first 5–7 days following surgery. The same scale will be used by physiotherapists to assess pain pre and post-physiotherapy treatment. In addition patients will be familiar with these scales and will use them to rate their pain in a Pain/Medication/PT compliance journal throughout the study. The NRS has been translated into several languages. Guidelines accompany both the NRS and Faces Pain Scale-Revised ensuring that they are administered in a uniform fashion [75].

**Medication dosages **are extracted from the inpatient medical record and recorded on custom data collection forms. The pain scores from the inpatient and outpatient period are also transcribed to this form.

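### The primary pain comparison takes FPS-R or NRS scores into an unadjusted t-test, so any scale or age difference stays in the error term: lost precision, not bias

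*Protocol article*

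**What the plan says.** Section 14 (Statistical Analysis) lists three primary outcomes, the first being "pain measured by the FPS-r or NRS". The list of primary hypotheses in the same section ends by naming the two instruments as one measure: "Primary Outcome Measures: FPS-r/NRS, PedsQL, ROM". The method is "The primary analysis will be conducted using T-tests for continuous variables and chi-square and Fisher exact tests for categorical variables". No covariate or stratum is attached to the primary tests. Age appears as a stratifying variable only under Secondary Analysis.

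Section 8 (Pain Management Protocol) says pain is scored on a common ten-point scale, "either Faces Pain Scale revised or the Numerical Rating Scale". Section 11 (Outcome Assessment) says the FPS-R "is a reliable and valid pain scale for younger children", without giving an age cut-off. The inclusion criteria admit ages 5 to 21.

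Randomisation (section 2) is blocked within site. The patient strata in section 1 are indication and severity. Neither age nor pain scale is balanced by design.

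**The concern.** One outcome is recorded on either of two instruments, and the choice of instrument goes with age. Equal length does not show that a chosen face and a chosen number have the same mean for the same pain. Even if the scales were interchangeable, young children and young adults may report different levels of pain after the same surgery. A two-sample t-test on the combined scores treats any such difference as random variation between patients.

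Relief of early post-operative pain is the objective stated at the end of the Background, and pain scores carry two of the five primary hypotheses. Avoidable residual variance lowers the chance of detecting a real analgesic effect on that outcome. A single combined mean is also harder to interpret than means shown within each scale.

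**Working it through.** **Inputs from the article (Sample size, section 14).** 75 per group, effect size 0.45, alpha 0.05, stated power 80%. Sidedness is not stated; two-sided is assumed. The only SD given is 15, for the PedsQL.

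**Inputs that are assumptions.** The share *p* of children on the FPS-R (0.20 to 0.50), the mean gap *g* between the two scale/age groups in within-scale SD units (0.25 to 1.0), and a true pain effect of 0.45 within-scale SD. The article ties 0.45 to the PedsQL; it is borrowed here for pain.

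**Step 1: reproduce the stated power.** By the normal approximation, power = Φ(d·√(n/2) − 1.96) = Φ(0.45 × √37.5 − 1.96) = Φ(0.796) = 78.7%. The noncentral t gives 78.2%. Both are within 2 points of the stated 80%.

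**Step 2: variance left in the residual.** With within-scale SD 1, the SD seen by the unadjusted test is √(1 + p(1−p)g²). The effect size becomes 0.45 divided by that. At p = 0.5 and g = 1 the SD is √1.25 = 1.118 and d = 0.402. Power is then Φ(0.402 × √37.5 − 1.96) = Φ(0.50) = 69.3%.

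**Step 3: the range (normal approximation, 75 per group).**

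| Gap g (SD) | Power of plain t-test, p from 0.20 to 0.50 | Loss from 78.7% (points) | n per group for 80% power |
|---|---|---|---|
| 0 | 78.7% | 0 | 78 |
| 0.25 | 78.1-78.3% | 0.4-0.6 | 79 |
| 0.5 | 76.2-77.1% | 1.6-2.5 | 81-83 |
| 0.75 | 73.2-75.2% | 3.5-5.5 | 85-89 |
| 1.0 | 69.3-72.5% | 6.2-9.4 | 90-97 |

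**Step 4: simulation of the two analyses** (20,000 trials per setting, p = 0.35).
- Gap 1 SD, true effect 0.45: power is 70.1% for the plain t-test and 78.3% for a linear model with scale as a factor. The mean estimate is 0.45 for both.
- Gap 1 SD, no effect: the rejection rate is 5.3% for both.
- No gap, true effect 0.45: power is 78.2% and 78.0%, so adjusting costs almost nothing when it is not needed.

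**Step 5: the other way to read 0.45.** If 0.45 is taken in units of the combined SD, the plain test keeps 78.7% and adjustment adds power. At a gap of 0.5 combined SD, power rises to 80.3-81.2% for p from 0.20 to 0.50. The direction of the advice is the same.

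**The case against.** The best defence is that an unadjusted t-test in a randomised trial is valid, and that covariates and the handling of two instruments are often left to an analysis plan that is not shown here. The article never says in so many words that raw scores are combined without regard to scale. The scales share a ten-point range, and section 11 adds "Guidelines accompany both the NRS and Faces Pain Scale-Revised ensuring that they are administered in a uniform fashion". The rule for which child uses which scale may sit in the study manual.

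Much of this stands. The test is valid, nothing in the article is contradictory, and a shared range may keep the gap small. Combining the scores is nevertheless the natural reading of an outcome listed as FPS-R or NRS. The article also does more than stay silent: it names the primary test without adjustment and uses age only in secondary analyses. The point is about that stated choice.

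Several stronger readings are not supported:
- **That the result would be biased or the test invalid.** Randomisation prevents this, and the simulation shows the same mean estimate and type I error with or without adjustment.
- **That the post-operative PCA protocols decide which scale a child gets.** In section 8 that phrase leads into the assessment times; it most naturally governs how and when pain is scored.
- **That the scale is already known for every child.** The article does not say it is recorded, so the fix must include recording it.
- **That consistent use of a scale is ignored.** Section 11 already has the physiotherapists use the same scale as nursing and says patients will use these scales in the journal.
- **That the loss is large.** A loss equal to about 20 of 150 children follows if 40% are on the FPS-R and the gap is 0.8 SD: 1 + 0.24 × 0.64 = 1.154, and 150 − 150/1.154 ≈ 20. No figure in the article supports a gap of that size.

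**Conclusion.** The point holds as a minor improvement in efficiency. The stated primary pain test leaves any mean difference between scale or age groups in the error term, and the documents give no sign that it is removed. Type I error and the expected estimate are unaffected.

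The loss rests wholly on assumed values of the FPS-R share, the gap and the pain effect. It may be under 1 point of power at a gap of 0.25 SD, and it reaches 6-9 points only at 1 SD. The documents cannot show where in that range the trial lies. The reason to act is that the remedy is almost free and that the trial starts at about 78% power, with no slack against its stated 80%.

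**What to change.** In section 14, replace the plain t-test for the two primary pain comparisons with a linear model of pain on treatment, adjusted for the scale assigned to the child before randomisation. A comparison stratified by that scale would serve equally. Age is an acceptable alternative and is already available. Also tabulate pain by arm within each scale, so that a reader can see whether the treatment difference is similar on both.

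In section 8 or 11, record each child's assigned scale before randomisation. A scale chosen after surgery could depend on the child's condition and so on treatment, and would not be a safe adjustment variable.

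The cost is one sentence of analysis wording, one degree of freedom and one recorded field. No extra patients or visits are needed.

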#### Stratification by patient characteristic

Participants will be stratified according to three indications for treatment: simple lengthening, lengthening with deformity correction, and soft tissue correction. The amount of lengthening anticipated will be calculated both as an absolute value in cm as well as a percentage of the length of the bone to be lengthened. Amount of deformity correction will be calculated in number of degrees. Participants will be stratified to two categories according to the severity of the limb length discrepancy or deformity correction: < 20% or > 20% of the pre-operative values.

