### 2. Randomization

The randomization occurs at each site according to the procedure successfully used during the pilot. The bio-statistician consultant will generate a computerized block randomization schedule for each site ensuring an equal number of subjects in each group at each site. The coordinating site will provide each site with a set of sealed envelopes containing the randomization code for each patient, which will be opened only by the individual preparing the syringe. The patients will be randomly assigned to either the treatment group or the placebo group. Concealment of randomization will be enforced, so that individuals enrolling patients will be unaware of whether the next patient will be randomized to treatment or control [73,74].

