#### Secondary Analysis

Secondary longitudinal analyses will be carried out and include several time periods and compare additional variables as shown in the following table. Stratification by age or site of fixator or type of surgery (lengthening versus correction) will allow further analyses. T-tests and analyses by repeated measures will be used for the secondary analyses.

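### The primary analysis is fixed as unadjusted t-tests, which leaves site blocking and the pre-lengthening score unused and gives up precision, chiefly for PedsQL and ROM

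*Protocol article*

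**What the plan says.** Section 14, Statistical Analysis, of the protocol article sets the primary method: "The primary analysis will be conducted using T-tests for continuous variables and chi-square and Fisher exact tests for categorical variables". No site term, stratum or covariate is attached to it. Baseline enters that section only in the descriptive summaries: "The mean, median, standard deviation, and range of each variable and its change from baseline, measured on a continuous scale, will be presented".

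Three other parts of the document bear on this.

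- Section 11, Outcome Assessment, gives the general schedule: "The measures will be administered pre-lengthening, pre-distraction, mid-distraction, end distraction, mid-consolidation, pre-frame removal and 3 months post-frame removal". It refers to Table 1 for which tool is used at which phase.
- Section 2, Randomization, has the biostatistician prepare a "computerized block randomization schedule for each site ensuring an equal number of subjects in each group at each site".
- The section on stratification by patient characteristic states "Participants will be stratified according to three indications for treatment: simple lengthening, lengthening with deformity correction, and soft tissue correction", and then "Participants will be stratified to two categories according to the severity of the limb length discrepancy or deformity correction". It does not say whether these groupings govern randomisation or the analysis.

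The Secondary Analysis section adds: "Stratification by age or site of fixator or type of surgery (lengthening versus correction) will allow further analyses". Study centre and the severity category do not appear in any analysis that the article describes.

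**The concern.** The design provides two sources of precision that the stated primary test does not use. The first is blocking by site: the blocking balances the arms within centres, but a pooled t-test leaves between-site variation in its standard error. The second is the pre-lengthening value: where an outcome is measured before surgery and correlates with its later value, adjustment removes the explained part of the residual variance.

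At stake are wider confidence intervals and lower power than the collected data allow. Recruitment is limited, with about 75 potential participants a year across all six sites, so precision that needs no extra patients is worth having. It matters most for PedsQL, which is both a primary outcome and the basis of the Sample size section.

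The role of the declared strata is also unclear. One section stratifies by indication and severity, the randomisation section mentions site only, and the secondary analyses list age, site of fixator and type of surgery.

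**Working it through.** **Inputs from the document.** n = 75 per arm, effect size d = 0.45, alpha = 0.05, stated power 80% (Sample size section). Sidedness is not stated; two-sided is used here because one-sided gives 86.7%, which does not fit the stated 80%.

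**Inputs assumed.** The correlation r between the pre-lengthening value and the outcome, and the share R² of outcome variance lying between sites. The document gives neither.

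**1. The plan's own figure.** For an unadjusted comparison, power ≈ Φ(d·√(n/2) − 1.96).
- d·√(n/2) = 0.45 × √37.5 = 2.756
- Φ(2.756 − 1.96) = 78.7%; the exact noncentral t gives 78.2%

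This is close to the stated 80%, so the sample size was also planned without adjustment.

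**2. Adjusting for the pre-lengthening value.** The residual SD is multiplied by √(1 − r²), so the effective effect size is 0.45/√(1 − r²). The unadjusted sample giving the same precision is 75/(1 − r²) per arm.

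| r (assumed) | Effective d | Power, normal | Power, noncentral t | Equivalent n per arm |
|---|---|---|---|---|
| none | 0.450 | 78.7% | 78.2% | 75 |
| 0.3 | 0.472 | 82.4% | 81.9% | 82 |
| 0.5 | 0.520 | 88.9% | 88.5% | 100 |

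Confidence intervals scale by √(1 − r²): 0.954 at r = 0.3 and 0.866 at r = 0.5, that is about 5% and 13% narrower. Taking 7 further degrees of freedom for covariates (141 in place of 148) changes these powers by less than 0.1 percentage point.

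**3. Adjusting for site only.** With arms balanced within sites, the treatment difference varies with the within-site variance (1 − R²), while the pooled t-test estimates its standard error from the total variance.
- True two-sided alpha of the t-test = 2[1 − Φ(1.96/√(1 − R²))]
- Power of the t-test = Φ((2.756 − 1.96)/√(1 − R²))
- Power with site in the model = Φ(2.756/√(1 − R²) − 1.96)

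| R² (assumed) | True alpha, t-test | Power, t-test | Power, site-adjusted | Gain |
|---|---|---|---|---|
| 2% | 0.048 | 78.9% | 79.5% | 0.6 points |
| 5% | 0.044 | 79.3% | 80.7% | 1.4 points |
| 10% | 0.039 | 79.9% | 82.8% | 2.8 points |

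The right comparison is with the t-test's own power under blocking, which is slightly above 78.7%. The site gain is therefore small.

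**4. Would a t-test on change scores do as well?** The SD of a change is √(2(1 − r)) times the outcome SD. At r = 0.5 this factor is 1 and power stays at 78.7%. At r = 0.3 it falls to 64.4%. Reading the plan as a change-score test does not recover the loss at these correlations.

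**5. Which outcomes benefit.** PedsQL and range of motion can have a pre-lengthening value. The 10-day narcotic total cannot. A pre-operative pain score may predict early post-operative pain only weakly, so r there may be at or below the low end of the range.

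**The case against.** The strongest objection is that nothing here is an error. Under randomisation the unadjusted t-test is unbiased, and chance imbalance is already covered by its standard error. Covariate sets are often left to an analysis plan, and this is a condensed article. The first part stands in full. The second stands only partly: the article does not leave the method open but names the t-test as primary, and its power figure matches an unadjusted comparison.

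The size of the gain rests on an assumed correlation. That stands, so it is shown as a range; at r = 0.3 the gain is under 4 points. It is also uncertain which tools are given before lengthening. The schedule sentence is general, Table 1 is not shown, the family impact scale is given only at the end, and range of motion is described as recorded from post-operative day 2. The planned change-from-baseline summaries suggest that baselines exist, but the recommendation has to be limited to outcomes for which one is measured.

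A reader might go further and infer that the trial is underpowered. The document does not support that: 78% is close to the stated 80%, and the Sample size section's own 7.5 points with SD 15 is d = 0.50, for which 75 per arm gives 86.5%.

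A reader might also infer that indication and severity were meant as randomisation strata and were dropped, or that crossing them with site would leave tiny cells. The stratification section never says that they enter randomisation, and type of surgery in the secondary analyses overlaps with indication. Only the ambiguity can be raised.

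**Conclusion.** The point holds as a loss of efficiency that can be avoided. It is not a question of bias or validity. For PedsQL, and for range of motion where a pre-lengthening value exists, baseline adjustment at 75 per arm and d = 0.45 would raise power from 78% to about 82% (r = 0.3) or 89% (r = 0.5), the same as having 82 or 100 patients per arm. These figures depend on the assumed r. The site term adds roughly 0.6 to 2.8 points for an assumed 2 to 10% of variance between sites, and it brings the test back to its nominal level. Narcotic use gains nothing from baseline, and early post-operative pain may gain little. The change is worth making because the data are already scheduled for collection, but the trial remains interpretable without it.

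The unclear role of indication and severity is a separate matter of wording, and the document does not settle which reading is right.

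**What to change.** - In section 14, define the primary analysis of each continuous outcome as a prespecified linear model (ANCOVA) with treatment, site and, where it is measured, the pre-lengthening value of that outcome. Indication and severity category may be added as covariates. For the narcotic total, the model has treatment and site without a baseline term.
- Keep the t-test as a sensitivity analysis.
- Settle this before the interim look at 75 patients, and use the same model there.
- Separately, reconcile the sections on stratification, randomisation and secondary analysis: state whether indication and severity restrict the randomisation, are analysis factors, or both, according to what was actually done.

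The cost is a change of wording in the analysis section and some statistical programming. No new data or patients are needed. A few degrees of freedom are spent, which is negligible at 150 patients, though the covariate list should stay short because the interim has half that number.
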